### Type and design of the study

4.1

The present study is a randomized controlled experiment in N = 100 SUD- inpatients during a therapeutic community treatment with one intervention group that will receive an additional 6-week smoking cessation intervention and one control group that will receive treatment as usual. The study design consists of a 2 x 2 mixed subject design with repeated measures for the biological analyses and a 2 x 3 mixed subject design with repeated measures for the psychobehavioural analyses (see **Table 1**). In both groups, an examination of metabolic and gut microbial profiles, as well as psychological variables, will take place. Biological parameters will be ascertained from blood and stool specimens for nuclear magnetic resonance (NMR) spectroscopy metabolomic analyses and from stool specimens for 16s-mRNA (hypervariable V3-V4 regions) sequencing and subsequent gut microbial profiling. Psychobehavioural and biological data will be collected pre & post smoking cessation, and additionally, there will be a follow-up measurement of the psychobehavioural variables 3 months upon completion of the study (see **Figure 3**: Consort Flow Chart for further illustration).

**Table 1 T1:** Overview of the statistical design.

Study group	Pre- intervention baseline	Post- intervention after 6 weeks	Follow- up after 3 months
Intervention Group (N = 50)	Psychobehavioural Data	Psychobehavioural Data	Psychobehavioural Data
	Metabolic/Microbial Data	Metabolic/Microbial Data	
Control Group (N = 50)	Psychobehavioural Data	Psychobehavioural Data	Psychobehavioural Data
	Metabolic/Microbial Data	Metabolic/Microbial Data	

green cells: biological data; light brown cells: self-report data.

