### Recruitment

4.2

The recruitment and examination will involve patients from the association “Grüner Kreis”, who are housed at the Johnsdorf facility. All patients are diagnosed with a form of SUD (F1x.x) by a licensed psychiatrist according to the International Classification of Diseases version 10 (98). Furthermore, participants have to explicitly state that they want to quit smoking. After administering the psychological questionnaires and collecting demographic data, patients will be randomly assigned to either the intervention or control group. The allocation to the groups will be carried out using computer-assisted block randomization (https://www.randomizer.org). The location for the examinations (blood and stool samples) is the Otto Loewi Research Center at the Medical University of Graz. The transfer of participants (Johnsdorf facility – Otto Loewi Research Center/Med Uni Graz) will be carried out by the association’s own buses from Grüner Kreis. Upon completion of data collection, the intervention group will undergo a 6-week smoking cessation program, while the control group will only receive treatment as usual. After the intervention phase, participants will again complete psychological questionnaires, and blood and stool samples will be collected at the Otto Loewi Research Center. Three months later, a follow-up assessment of the psychobehavioural variables will be conducted.

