### Intervention

4.3

During the inpatient stay at the ‘Grüner Kreis’ community, the patients will be allocated to an intervention group and a control group. Patients of the intervention group will take part in an additional 6-week behavioural therapy program for smoking cessation. Patients of the control group will undergo treatment as usual. The standard treatment within this therapeutic community—which all participants will receive—consists of group therapy (once a week), individual psychotherapy (once a week), counseling by social workers, psychiatric consultations, as well as sport-, art- and work therapy. For further information on the principles of therapeutic community-based addiction treatment, see, e.g., DeLeon & Unterrainer (36).

The “smoke free in 6 weeks” program is a standardized behavioural therapy intervention (see Batra & Buchkremer (99) for detailed instructions) that takes place once a week for 1.5 hours over 6 weeks and is provided by the Austrian health insurance provider *Österreichische Gesundheitskasse* (ÖGK). Held in the therapeutic community, it will employ principles of cognitive-behavioural therapy (CBT) coupled with personalized recommendations for nicotine replacement. The Austrian health insurance standard for therapy will be guiding the program’s content, which is tailored for inpatient clients. Specifically, the following interventions based on CBT techniques will be applied in the weekly group sessions consisting of 10 to 15 participants: Psychoeducation including information on tobacco addiction, health risks, advice on relapse prevention and the handling of craving, motivation building, behavioural observation, setting a personal quit-smoking day, behaviour modification through the development of alternative actions, training of progressive muscle relaxation, strengthening of self-efficacy and information on the topics of physical activity and nutrition. Finally, to increase intrinsic motivation, each session will include an analysis using a calibrated carbon monoxide measurement. The primary aim is to help clients achieve smoking cessation, favouring this approach over gradual reduction methods. To support ongoing abstinence and motivation, participants will be directed to additional resources such as the Smoke-Free App, Smoke-Free Phone, and regional outpatient cessation services. This program will be led by a clinical psychologist who is specifically trained in conducting the program.

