### Inclusion and exclusion criteria

4.5

*Inclusion Criteria:* Participants must provide informed consent. They must have a diagnosis of a form of substance use disorder (F1x.x) by a licensed psychiatrist according to ICD-10 (98). Participants must be at least 18 years old, can be of either sex, and must have sufficient knowledge of the German language. All participants must explicitly express their willingness to quit smoking. A minimum duration of abstinence from the primary substance and stable dosage of long-term medications for at least 3 months prior to inclusion is mandatory.

*Exclusion Criteria* include lack of consent, age below 18, or inability to provide informed consent. Participants with acute psychotic symptoms or acute suicidal tendencies are also excluded. Further exclusions are cardiovascular disease, pregnancy or breastfeeding, severe mental or organic illnesses (such as epilepsy, brain tumours, recent major surgery), tumour diseases, dementia (Mini Mental Score <20), severe autoimmune diseases or immunosuppression, acute infections, or acute diarrhea. Individuals with prior gastrointestinal surgery (except appendectomy), probiotic intake within the last 6 months, or those consuming dietary supplements, probiotics, antibiotics, or prebiotic supplements during the study will also be excluded.

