A-priori sample size calculations were performed with G-Power (108) (version 3.1.9.6), for a mixed-design ANOVA with one interaction between group (2 groups) and assessments (2 repeated measurements). Considering the effects mentioned above, the mixed-design ANOVA was set rather conservatively for a medium effect size (Cohen’s F = 0.25), a statistical Power (1-β) of 0.9, a α of 0.05, an intra-correlation coefficient of 0.5 and nonsphericity correction of 1, resulting in a minimum sample size of 46 subjects per group, and a critical F = 4.06. Adjusting for expected attrition of about 10%, a total sample size of size of 100 is set. The many (mostly biological) variables measured in this study will expectably require statistical corrections; this will also be compensated by statistical methods exceeding classical linear approaches, namely machine learning feature detection and modelling methods (109).

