#### Diet

4.7.2

Nutritional variables will be a highly relevant source of variance in the study, particularly for metabolome and microbiome parameters. Food compounds, energy and nutrient intake will therefore be analysed from food frequency data by the nutritional software nut.s ^®^v1.32.95 (110). Nutrient intake will be adjusted for total energy intake, and nutrients with excessive missings will be excluded.

It appears inadequate to consider dietal factors merely as control variables, as nicotine is known to interact strongly with regulation of appetite and satiety, and smoking cessation usually goes along with a weight-gain (111). Nutritional variables are therefore candidate mediator or explanatory variables, and it is important to quantify how much of the group effects will be explained by energy intake and nutrients. For this purpose, the variance explained by nutrition will be quantified via Partial distance-based redundancy analysis (db-RDA) and/or PERMANOVA (for both microbial beta diversity and metabolite distances). Variance will be decomposed by stepwise separation of variance explained by group, variance explained by nutritional variables (energy, nutrients, selected compounds), control variables (see below), and shared variance.

Additional adjustment analyses will be performed in candidate biomarkers of smoking cessation group effects emerging from metabolome and microbiome analyses (at the level of metabolites, or specific bacterial taxa). Linear mixed effects models (lme4 package in R (112)) will be iteratively tested (total effect vs. nutrition-adjusted models) for shrinked coefficients of group effects for this purpose.

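### The eligibility rule on supplements, probiotics, antibiotics and prebiotics taken during the study acts mainly after randomisation and covers the whole person, so it could break the randomised comparison for the psychobehavioural outcomes

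*Protocol article*

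**What the plan says.** Section 4.5 (Inclusion and exclusion criteria) contains two rules with different time windows. One looks back from entry: "probiotic intake within the last 6 months". The other looks forward: "those consuming dietary supplements, probiotics, antibiotics, or prebiotic supplements during the study will also be excluded". The second is not limited to particular outcomes or analyses.

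Section 4.2 (Recruitment) gives the order of events: "After administering the psychological questionnaires and collecting demographic data, patients will be randomly assigned to either the intervention or control group". The programme, the post-intervention assessment and the later follow-up all come after that.

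Table 1 in section 4.1 shows biological samples at baseline and at 6 weeks only. The psychobehavioural outcomes continue: "there will be a follow-up measurement of the psychobehavioural variables 3 months upon completion of the study".

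Two passages bear on whether exposure could differ by arm. The intervention sessions in section 4.3 include "strengthening of self-efficacy and information on the topics of physical activity and nutrition". Section 4.7.2 (Diet) states that "nicotine is known to interact strongly with regulation of appetite and satiety, and smoking cessation usually goes along with a weight-gain", and on that ground treats nutritional variables as possible mediators, not merely as controls.

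**The concern.** An eligibility criterion should be decidable at entry. This one depends on what participants do later, so it can remove people who have already been randomised. The groups then compared are not the groups that were allocated, and randomisation no longer guarantees that they are alike. Section 4.7.7 names randomisation as the first safeguard against bias.

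The rule is also wider than its evident purpose. An antibiotic course or a supplement can disturb the stool microbiome and the metabolome. It does not invalidate a questionnaire score, a report of abstinence or a relapse record. Removing the person loses both kinds of data. If follow-up stops at exclusion, the later outcomes cannot be recovered.

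For supplements there is a tension with the plan's own reasoning. Section 4.7.2 regards nutrition as something cessation may change and through which it may act. Dropping people for supplement use after allocation conditions on a variable of that kind.

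**Working it through.** **1. When the rule can act.** Three windows follow from sections 4.1, 4.2 and 4.5.

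- Entry to randomisation: short; exposure could be checked before allocation.
- Randomisation to the 6-week samples: after allocation; exposure can affect the second biological sample.
- 6-week samples to follow-up three months later: after allocation; no biological sample remains to be affected.

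Taking three months as about 13 weeks, the third window is 13 / (6 + 13) = 68% of the time after allocation. If the study is taken to run to the last follow-up, most of the period in which the rule can act has no biological sample to protect.

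**2. The plan's own sample size figure.** Inputs from section 4.7.1: "medium effect size (Cohen’s F = 0.25" and "a statistical Power (1-β) of 0.9, a α of 0.05, an intra-correlation coefficient of 0.5 and nonsphericity correction of 1", with two groups and two measurements. In the G*Power default form for a within-between interaction:

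λ = f² × N × m / (1 − ρ) = 0.0625 × N × 2 / 0.5 = 0.25 N, with degrees of freedom 1 and N − 2.

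- N = 44: λ = 11.0, power 0.8997.
- N = 46: λ = 11.5, critical F = 4.06, power 0.91.
- N = 92: λ = 23.0, critical F = 3.95, power 0.997.

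The stated 46 and critical F of 4.06 therefore reproduce as a total, not as a number per group. That is a separate matter; here it matters only because it shows how much room the trial has at f = 0.25.

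**3. Effect of further exclusion on power.** Start from 100 randomised with 10% attrition, leaving 90. The further exclusion rates are assumed.

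| Further exclusion | N left | Power at f = 0.25 |
|---|---|---|
| 0% | 90 | 0.997 |
| 10% | 81 | 0.994 |
| 20% | 72 | 0.987 |
| 30% | 63 | 0.974 |

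**4. Possible bias.** Let e₁ and e₀ be the excluded shares in the intervention and control arms, and let D be the amount, in SD of change, by which retained participants exceed excluded ones. In each arm, the retained mean minus the full mean is e × D. With the same D in both arms the bias is (e₁ − e₀) × D. Start from 45 per arm, so nᵢ = 45 × (1 − eᵢ) and SE = √(1/n₁ + 1/n₀). The actual type I error of a nominal 5% two-sided test follows from bias / SE (normal approximation). All values of e and D are assumptions.

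| e₁ vs e₀ | D | Bias (SD) | Type I error |
|---|---|---|---|
| 10% vs 10% | any shown (0.3–0.8) | 0 | 5.0% |
| 15% vs 5% | 0.5 | 0.10 × 0.5 = 0.05 | 5.6% |
| 20% vs 5% | 0.8 | 0.15 × 0.8 = 0.12 | 8.3% |
| 30% vs 10% | 0.8 | 0.20 × 0.8 = 0.16 | 10.3% |

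For the second row: n₁ = 38.25, n₀ = 42.75, SE = 0.223, bias / SE = 0.225.

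**The case against.** Several points weigh against a stronger version.

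*Loss of power.* A reader might infer that the exclusions erode a sample with no margin. On the plan's own basis they do not: the table above shows a loss of about 0.02 at 30% exclusion. With a smaller effect the loss would be larger. At the 0.70 SD the article quotes for its pilot, taken as a two-group difference, power falls from 0.91 at 45 per arm to 0.83 with 20% loss. But the plan sizes the trial on f = 0.25, and that gap is a question about the planning value, not about this clause.

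*Difference between arms.* A reader might infer that exclusion will depend on arm. The document makes this possible, not established. Nutrition is one topic among many in section 4.3, nothing there recommends supplements, and section 4.7.7 houses everyone in one facility with the same meals, which tends to limit differences. A chain from smoking status to infection to antibiotic courses has no support in the text.

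*Deletion of data.* A reader might infer that the plan says psychobehavioural data are discarded. It does not. Section 4.5 does not say when exclusion takes effect or what happens to data already collected, and analysis sets may be defined in a document not shown. The inference rests on the unrestricted wording.

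*Length of the window.* Section 4.1 places follow-up after completion of the study, so the period meant could end with the 6-week assessment. The clause would then not reach exposures after the last sample. It would still act throughout the six weeks after allocation.

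*Purpose.* Protecting the interpretation of largely exploratory biological analyses is legitimate. That supports a rule for those analyses, not for the questionnaires.

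These points limit the size and certainty of the concern. They do not remove it: a literal reading still excludes randomised people from outcomes that the exposure does not affect.

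**Conclusion.** The concern holds as a flaw in how the criterion is drawn. As written, it makes eligibility depend on conduct after randomisation and applies to the whole person. The harm is possible bias and loss of the randomised comparison for the psychobehavioural outcomes, not loss of power.

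The size cannot be fixed from the document, because it gives neither exposure rates nor a split by arm. The three unequal scenarios shown give 0.05 to 0.16 SD of bias and a type I error of 5.6% to 10.3%. Equal shares with the same outcome difference in both arms give none. The conclusion also assumes that exclusion means removal from the analysis, which is the plain reading but is not spelled out. The clause should be fixed, with medium confidence.

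**What to change.** 1. In section 4.5, limit the criterion on supplements, probiotics, antibiotics and prebiotics to use before randomisation.
2. After randomisation, record the date and type of any such exposure and report it by arm.
3. State that all randomised participants stay in follow-up and in the psychobehavioural analyses, in the arm to which they were allocated.
4. Handle exposure only within the microbiome and metabolome analyses: report results with and without samples taken after exposure, and name in advance which is primary. Which to choose is open to debate, and the point does not depend on it.

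The cost is a short amendment, a simple exposure log and slightly more analysis work. It should be done before any randomised participant is removed under the present wording, since outcomes not collected cannot be restored.

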### Risk assessment

4.6

Providing a stool sample carries no risk. However, blood sampling can result in a bruise (hematoma), and depending on the condition of the veins, it can be more or less painful. This will be performed by an experienced study physician in accordance with WHO guidelines (107), who will also offer immediate support if necessary. Completing online-questionnaires can lead to fatigue and tiredness. However, participants have the option to take breaks or to interrupt or discontinue completing the questionnaires at any time. Therefore, the risk-benefit ratio is considered positive, and the risk of the study is considered as low for participants.

### Statistical analyses

4.7

#### Power calculation

4.7.1

As the approach of this study is biopsychological, we drew on selected data from different domains from relevant studies to estimate effect sizes: metabolic differences between active smokers and former smokers, changes in gut microbiome parameters, and a psychological variable during smoking cessation. A recent multi-omics study (27) compared metabolite levels between cigarette smokers, e-vapers, and former smokers. N-acetylputrescine metabolite concentrations showed a clear association with smoking-related metabolic variation. Because raw metabolite concentrations were not given, effect sizes of standardized differences between cigarette smokers and former smokers were estimated from the correlation between N-acetylputrescine and the combustion-related principal component (PC1), giving an estimated approximate standardized mean difference of Cohen’s d ≈ 0.73, indicating a medium-to-large effect size. This suggests substantially higher N-acetylputrescine levels in cigarette smokers compared with former smokers, consistent with persistent alterations in polyamine metabolism in active smoking.

For microbiome changes after smoking cessation, Sublette et al. (67) reported increased abundances of Bacteroidetes in successful abstainers (n=14 of 26 at week 12). The increase in relative abundance of Bacteroidetes from baseline to 12 weeks in smokers who quit compared with those who continued smoking corresponded to an approximate standardized effect size of r ≈ 0.41 (based on regression estimate β = 7.4 percentage points, SE = 3.5), suggesting a moderate effect.

Psychological self-efficacy increased during smoking cessation in a pilot study by our own research group (55) and showed a medium-to-strong effect (η_p_^2^ = .11; converted to Cohen’s d ≈.70).

A-priori sample size calculations were performed with G-Power (108) (version 3.1.9.6), for a mixed-design ANOVA with one interaction between group (2 groups) and assessments (2 repeated measurements). Considering the effects mentioned above, the mixed-design ANOVA was set rather conservatively for a medium effect size (Cohen’s F = 0.25), a statistical Power (1-β) of 0.9, a α of 0.05, an intra-correlation coefficient of 0.5 and nonsphericity correction of 1, resulting in a minimum sample size of 46 subjects per group, and a critical F = 4.06. Adjusting for expected attrition of about 10%, a total sample size of size of 100 is set. The many (mostly biological) variables measured in this study will expectably require statistical corrections; this will also be compensated by statistical methods exceeding classical linear approaches, namely machine learning feature detection and modelling methods (109).

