#### Statistical analyses of psychological variables

4.7.4

The statistical analyses will be performed in SPSS version 29 (IBM) for general procedures, while specific regression models are handled in R (R core team (121)). For example, t-tests will be carried out for independent and paired comparisons of means between and within groups at different times, respectively, assuming that the continuous data are normally distributed. Chi-square and Fisher’s exact tests, the latter in cases of smaller sample sizes, will be conducted in order to test the associations between categorical variables. The Friedman test shall be used in analyzing non-parametric repeated measures. The main effects of the intervention, time effects, and group x time interaction will be tested using a 2 × 3 two-way repeated measures ANOVA design (group x time), using the Greenhouse-Geisser correction in cases when the sphericity assumption will be violated. The level of significance will be α = 0.05, two-tailed, using Bonferroni adjustment for multiple comparisons. In addition, a repeated measures proportional odds logistic regression model using a generalized estimating equation (GEE) will be applied, assessing the intervention’s effect on CPD treated as an ordinal variable. The GEE model, computed in R using the `repolr` package (122), will contain robust variance estimators that take into account within-subject correlations (**Table 2**).

**Table 2 T2:** Summary of statistical methods and outcomes.

Outcome variable	Domain	Statistical method	Software
Self-efficacy, craving, psychiatric scores	Psychobehavioural	Repeated measures ANOVA, t-tests, Friedman test	SPSS
Cigarettes per day (ordinal)	Psychobehavioural	GEE (Proportional odds model)	R (repolr)
Bacterial diversity indices	Microbiome	Kruskal-Wallis, ANOSIM, db-RDA	R, QIIME
Taxonomic composition	Microbiome	MaAsLin2, ANCOM, LEfSe	QIIME2, R
Metabolite concentrations	Metabolic	PCA, O-PLS-DA, correlation analyses	NMR tools, R
Cross-domain associations	Combined (exploratory)	Correlation and regression	R

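### The stated power inputs give 46 subjects in total, not 46 per group; f = 0.25 exceeds the pilot effect; and the 90% power does not carry over to the biological arm comparisons

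*Protocol article*

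**What the plan says.** Section 4.7.1 starts from three effects. The first is a metabolite difference of d ≈ 0.73 between cigarette smokers and former smokers. The second is a microbiome change of r ≈ 0.41 "in smokers who quit compared with those who continued smoking", from a study with "successful abstainers (n=14 of 26 at week 12". The third is the group's own pilot result for self-efficacy, partial η² = .11, converted to d ≈ .70.

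The sample size is calculated "for a mixed-design ANOVA with one interaction between group (2 groups) and assessments (2 repeated measurements". In view of the three effects, "the mixed-design ANOVA was set rather conservatively for a medium effect size" (f = 0.25), with power 0.9, "a α of 0.05, an intra-correlation coefficient of 0.5 and nonsphericity correction of 1". The stated result is at least 46 per group and critical F = 4.06, raised to 100 in total for about 10% attrition. The section expects statistical corrections for the many variables, and adds that "this will also be compensated by statistical methods exceeding classical linear approaches", meaning machine learning.

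Section 1.6 gives the pilot statistic as F(1,53) = 5.86 and says that the pilot was not randomised. Section 4.7.3 plans intervention-versus-control comparisons for the microbiome.

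**The concern.** Three things in the power statement do not fit together.

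- The critical F belongs to a different sample size from the one reported beside it.
- The effect size described as a cautious step down from the listed effects is a step up from the only one measured on a planned trial outcome as a group-by-time interaction.
- Two of the three listed effects are differences by smoking status, while the trial will compare arms in which only some of the intervention group will have quit. Controls may quit too, since every participant must want to stop smoking (sections 4.2 and 4.5).

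A reader who takes the 90% at face value would treat a null arm comparison of metabolites or taxa as more informative than it is. Someone who noticed only the first inconsistency might also conclude that half the sample would do.

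**Working it through.** **1. Reproducing the stated figure.** Inputs from section 4.7.1: f = 0.25, ρ = 0.5, m = 2 assessments, 2 groups, nonsphericity 1, α = 0.05, power 0.90. For the within-between interaction under G*Power's default option, the noncentrality is λ = f²·N·m/(1−ρ) = 0.0625·N·2/0.5 = 0.25·N, with 1 and N−2 degrees of freedom.

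| Total N | df2 | Critical F | Power at f = 0.25 |
|---|---|---|---|
| 44 | 42 | 4.07 | 0.8997 |
| 46 | 44 | 4.06 | 0.912 |
| 92 | 90 | 3.95 | 0.997 |

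The smallest even N reaching 0.90 is 46 in total (23 per group), and its critical F is the stated 4.06. Other readings of the inputs do not give 92: λ = f²·N needs 172, λ = f²·(N−2) needs 174, the between-group test needs 130, and ρ = 0 needs 88. Their critical F values lie between 3.90 and 3.95.

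**2. What f = 0.25 means in that metric.** f²·m/(1−ρ) = 0.0625·4 = 0.25, so partial η² = 0.25/1.25 = 0.20. The standardised difference in change is 2·√0.25 = 1.0. At ρ = 0.5 the SD of change equals the raw SD, so this is 1.0 SD.

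**3. The pilot on the same scale.** 0.11/0.89 = 0.1236, so d = 2·√0.1236 = 0.70 and f = √(0.1236·0.5/2) = 0.176. The reported F gives slightly less: partial η² = 5.86/(5.86+53) = 0.0996, so d = 0.665; or 2·√(5.86/55) = 0.653 with 55 participants in equal groups.

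**4. Power of the planned sample for one outcome.** 50 per arm less 10% leaves 45 completers per arm. Two-sided 0.05, noncentral F on change:

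| Difference in change (SD) | Power, 45 per arm |
|---|---|
| 0.70 (pilot, as converted) | 0.91 |
| 0.665 / 0.653 (pilot, from F) | 0.88 / 0.86 |
| 0.69 | 0.90 |
| 0.60 | 0.80 |

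With 23 per arm, power at 0.70 SD would be 0.64.

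**5. Biological inputs as arm differences.** r = 0.41 converts to d = 2·0.41/√(1−0.41²) = 0.90. If the effect occurs only in quitters, the arm difference is d × (quit rate in intervention − quit rate in control). The protocol gives no expected quit rate for either arm. As an assumption, take 14/26 = 54% from the cited microbiome study for the intervention arm and 0–10% for control. The metabolite d is cross-sectional and is treated here as a difference in change.

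| Input | Quit-rate difference | Arm difference | Power, 45 per arm |
|---|---|---|---|
| d = 0.73 | 0.54 | 0.39 | 0.46 |
| d = 0.73 | 0.44 | 0.32 | 0.33 |
| d = 0.90 | 0.54 | 0.49 | 0.63 |
| d = 0.90 | 0.44 | 0.40 | 0.46 |

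Conversely, reaching 0.69 SD would need a quit-rate difference of 0.69/0.73 = 95 percentage points for the metabolite input, or 0.69/0.90 = 77 for the microbiome input.

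**The case against.** The strongest reply is that the sample is sound whatever the wording. Reporting 46 in total as 46 per group doubled the sample, and this offsets the optimistic input. A reader might infer from the 1.0 SD input that the trial is underpowered for the pilot effect. It is not: power there is about 0.91, and re-powering at 0.70 SD would need 44 per group, fewer than the 46 stated. This part of the reply stands in full.

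The protocol also calls much of its biological work exploratory (sections 2 and 2.1.2) and plans analyses against cigarettes per day and cessation success. That softens the consequence. It does not remove the fault, because section 4.7.1 uses the biological effects to justify a 90% figure and makes no allowance for incomplete quitting.

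The dilution figures do rest on assumed quit rates, the 54% coming from another study at week 12. Only the direction is firm.

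A reader might further infer that power for the psychological outcomes collapses because section 4.7.4 tests "using Bonferroni adjustment for multiple comparisons". The document does not support this. The phrase follows the repeated-measures ANOVA and may refer only to post-hoc contrasts, and no number of outcomes is given over which α would be divided.

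An instrumental-variable analysis of quitting might seem to undo the dilution. Its key assumption is doubtful here, since the programme also covers nutrition, physical activity and nicotine replacement (section 4.3), which can affect biomarkers without abstinence.

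**Conclusion.** The power statement is wrong as written, but the planned sample need not change. Two parts are firm and follow from the protocol's own figures: critical F = 4.06 belongs to 46 subjects in total, and f = 0.25 in that metric is 1.0 SD against the pilot's 0.70 SD. The protocol does not name the G*Power option, but of the readings tried only the default yields 4.06.

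The sample covers a self-efficacy effect of the pilot's size with almost no margin: 0.69 SD is detectable at 90%, and power is 0.86–0.88 if the pilot's reported F is used. The pilot was small and not randomised, so this is not conservative either.

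The 90% does not extend to arm comparisons of the biological outcomes unless quitting differs between arms by about 77 to 95 percentage points. The ranges 0.33–0.46 and 0.46–0.63 illustrate this under the stated assumptions; they are not predictions. Feature-selection methods do not restore the power of a multiplicity-corrected arm comparison.

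**What to change.** In section 4.7.1, with N left at 100:

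1. Reconcile 46 per group with critical F = 4.06, saying that the entered inputs return 46 in total and that the planned sample is larger.
2. Replace the sentence that calls the effect size conservative with: *45 completers per arm give 90% power for a between-arm difference in change of 0.69 SD (80% for 0.60 SD) for one outcome at two-sided 0.05.* Tie it to self-efficacy at 6 weeks, the outcome with pilot data.
3. State that the 90% does not extend to arm comparisons of the metabolic and microbiome outcomes, and show the diluted range with its quit-rate assumption.
4. Delete the claim that machine learning compensates for multiplicity correction.

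The cost is a few sentences and a less favourable stated power. Recruitment and procedures are unaffected.

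### The power calculation labels a total sample size of 46 as 46 per group, so the stated minimum, critical F and power do not belong to one design

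*Protocol article*

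**What the plan says.** Section 4.7.1 of the protocol article gives every input to the calculation. The software is named: "A-priori sample size calculations were performed with G-Power (108) (version 3.1.9.6"). The test is specified "for a mixed-design ANOVA with one interaction between group (2 groups) and assessments (2 repeated measurements"). The effect size was "set rather conservatively for a medium effect size (Cohen’s F = 0.25"), with "a statistical Power (1-β) of 0.9", "a α of 0.05", and "an intra-correlation coefficient of 0.5 and nonsphericity correction of 1". The output is reported as "resulting in a minimum sample size of 46 subjects per group, and a critical F = 4.06". The paragraph then moves to the enrolment target: "Adjusting for expected attrition of about 10%, a total sample size of size of 100 is set". Table 1 in section 4.1 shows this as 50 per group.

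Earlier in the same section, the article lists the effects that informed the choice of f. They include d ≈ 0.73 for a metabolite contrast between smokers and former smokers, and d ≈ 0.70 for self-efficacy in the group's own pilot study.

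**The concern.** G*Power reports a total sample size for repeated-measures ANOVA. The critical F printed beside the sample size depends on the error degrees of freedom, so it shows which total the program was working with. A value of 4.06 points to far fewer than 92 participants.

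This paragraph is the article's stated basis for enrolling 100. If its minimum is twice what its inputs give, an ethics committee or funder cannot tell from it what 92 or 100 participants deliver. Someone who notices the slip could also draw the wrong lesson and conclude that about half the planned enrolment would do.

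**Working it through.** **Inputs (all from section 4.7.1).** k = 2 groups, m = 2 measurements, f = 0.25, ρ = 0.5, ε = 1, α = 0.05, target power 0.90.

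**Formulas.** For the within-between interaction under G*Power's default effect-size option, with N the total sample size:

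- λ = f² · N · m · ε / (1 − ρ)
- df1 = (k − 1)(m − 1) = 1
- df2 = (N − k)(m − 1) = N − 2
- power = P(noncentral F(df1, df2, λ) > critical F)

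**Step 1: reproduce the printed output.**

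| Total N | Per group | λ | df2 | Critical F | Power |
|---|---|---|---|---|---|
| 44 | 22 | 11.0 | 42 | 4.07 | 0.8997 |
| 46 | 23 | 0.0625 × 46 × 2 / 0.5 = 11.5 | 44 | 4.06 | 0.912 |
| 90 | 45 | 22.5 | 88 | 3.95 | 0.997 |
| 92 | 46 | 23.0 | 90 | 3.95 | 0.997 |
| 100 | 50 | 25.0 | 98 | 3.94 | 0.999 |

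The smallest balanced total that reaches 0.90 is 46. It reproduces both printed figures, 46 and 4.06. A total of 92 reproduces neither the critical F nor the stated power.

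**Step 2: look for another setting that gives 46 per group.** Totals needed for 90% power, with their critical F:

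| Setting changed | Total N | Critical F |
|---|---|---|
| Effect size as in SPSS | 174 | 3.90 |
| Effect size as in Cohen | 172 | 3.90 |
| Between-group test | 130 | 3.92 |
| ρ = 0 | 88 | 3.95 |
| Three measurements | 36 | 3.13 |
| α = 0.10 | 36 | 2.86 |
| α = 0.025 | 54 | 5.33 |

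None gives 92 in total, and none gives a critical F of 4.06.

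**Step 3: what f = 0.25 means in this option.** In the 2 × 2 interaction, each cell departs by ±f·σ, so the between-arm difference in change is 4f·σ = 4 × 0.25σ = 1.0σ. The SD of change is σ·√(2(1 − ρ)) = σ·√(2 × 0.5) = σ. The calculation is therefore powered for a difference in change of 1.0 SD. In these units, with δ the standardised difference in change, λ = N·δ²/4.

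**Step 4: what the planned size delivers.**

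- 10% loss from 100 leaves 90 (45 per arm). Power reaches 0.90 at δ = 0.69, which is f = 0.69/4 ≈ 0.17.
- For δ = 0.70 (the pilot's d, read as a difference in change), λ at N = 90 is 90 × 0.49/4 = 11.0 and power is 0.907.
- For the same δ at N = 46, λ = 46 × 0.49/4 = 5.6 and power is 0.64.

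**Step 5: attrition.** From 92 required to 100 enrolled, the allowance is 1 − 92/100 = 8%. An exact 10% allowance would be 92/0.9 = 102.2, so 103. From the corrected 46 it would be 46/0.9 = 51.1, so 52.

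**The case against.** The best defence is that the slip is conservative and changes nothing in the trial. On the stated inputs, 52 enrolled would cover 10% attrition, and 100 are planned. Allocation, analysis and participant risk are unaffected. The conclusion a reader would draw, that 100 participants give about 90% power for an effect of the size cited, also survives for the pilot's d ≈ 0.70. All of this stands, and it is why the point is a correction to a stated figure and nothing heavier. It does not make the sentence correct, because the minimum, the critical F and the power still cannot all be true together.

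A second defence is that the 0.997 depends on G*Power's default effect-size option, which the article does not name. This also stands. Under the Cohen option, the same f = 0.25 gives power of only 0.66 at N = 92. The printed critical F of 4.06 does, however, identify the default option as the one used.

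Two stronger readings are tempting and are not supported:

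- **The attrition step is a further error.** A reader might note that 100 less 10% leaves 90, two below 92. But the text says about 10%, the 8% implied fits that wording, and power is 0.997 at both 90 and 92.
- **The trial is grossly oversized.** A reader might infer this from the factor of two and the 0.997. That figure applies to a 1.0 SD difference in change, which is larger than the effects of d ≈ 0.70 and d ≈ 0.73 that the article itself cites.

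**Conclusion.** The point holds as a mislabelled figure. The 46 is the total (23 per group), so the stated minimum is 92/46 = 2 times what the inputs give. At 46 per group, the critical F is 3.95 instead of 4.06 and the power is 0.997 instead of 0.9.

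The recalculation assumes G*Power's default effect-size option, which the printed critical F supports. The statement that 90 completers give about 0.91 power for the pilot effect also assumes that d ≈ 0.70 can be read as a standardised difference in change. The article gives it only as a conversion from partial eta squared.

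The planned 100 is defensible, but for a reason the paragraph does not give. This is a reporting correction and not a must-fix.

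**What to change.** Keep the enrolment target of 100 and amend section 4.7.1 as follows:

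1. Restate the output as 46 participants in total (23 per group), critical F(1,44) = 4.06, power 0.912, and name the effect-size option used.
2. Justify 100 by what it delivers: with about 10% attrition (45 per arm), 90% power at f ≈ 0.17 in the default option, a between-arm difference in change of about 0.69 SD. Compare this with the pilot's d ≈ 0.70, and say that the comparison reads that d as a difference in change.
3. If the 0.997 is quoted, say that it is conditional on the default option, in which f = 0.25 with ρ = 0.5 equals a 1.0 SD difference in change.
4. State that the correction is no ground for reducing enrolment, since 46 in total would give only about 0.64 power for d = 0.70.

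The cost is a wording change, with no extra participants and no change to design or analysis.
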